**Figure 4 F4:**
[figure not shown]
**Bar graph showing the patient’s risk of getting a myocardial infraction. **Shown are the patient’s current 5-year risk, the expected risk when goals are achieved for all risk factors, and the risk of a similar person without diabetes.

**Figure 5 F5:**
[figure not shown]
**Bar graph showing the patient’s possible risk reductions for each risk factor with accompanying questions. **Shown are the patient’s possible risk reduction when all or each of the separate risk factors would reach the recommended target values. Below the graph the accompanying questions asked in the decision aid are presented.

### Treatment options and treatment cards

On the final page or screen, the treatment options are summarised for those risk factors not yet at target level. Both lifestyle and medication options can be presented. The medication options are tailored to whether or not the patient is already treated and/or is already receiving maximum treatment. Maximum treatment is defined per risk factor as: using insulin with or without additional oral glucose-lowering medication, using three or more antihypertensive drugs, using a statin at maximum dosage. Possible pros and cons of the options are summarised. In addition, the healthcare providers can use a set of treatment cards during consultation to discuss and compare the benefits and risks of specific treatment options (Figure 6).

**Figure 6 F6:**
[figure not shown]
Example of treatment cards.

#### Control group

Patients in the control group will receive care as usual, including any education or information as deemed necessary by the healthcare provider.

### Effect modification

Effects of the decision aid may depend on characteristics of the patients that affect their involvement, understanding, and patient-provider communication about disease management. Therefore, the following characteristics will be included as possible modifying factors: age, gender, educational level, socioeconomic status, duration of diabetes, number and type of risk factors present, co-morbidity, and number of drugs used.

### Outcome measures

In correspondence with the aim of the decision aid, our primary outcome is empowerment of patients for making shared decisions about setting and achieving treatment goals [18]. As secondary outcomes, we include a set of additional patient outcome and process of care measures. These will provide insight into possible related positive and negative effects and a better understanding of how the novel approach may affect diabetes care.

Primary patient outcome:

a) diabetes empowerment (Diabetes Empowerment Scale, subscale ‘Setting and Achieving Goals’ [64])

Secondary patient outcomes:

b) satisfaction with diabetes care (PEQ-D [65])

c) beliefs about medication (BMQ [66])

d) negative emotions (PAID [67])

e) health status (EQ-5D [68])

f) predicted coronary heart disease risk [61])

Secondary process of care outcomes:

g) percentage of patients with (intensified) antihypertensive treatment after insufficiently controlled blood pressure levels

h) percentage of patients with (intensified) glucose-lowering treatment after insufficiently controlled HbA1c-levels

i) percentage of patients treated with lipid-lowering drugs

j) percentage of patients with (micro)albuminuria treated with a RAAS inhibitor

The Diabetes Empowerment Scale consists of three subscales measuring different aspects of patient empowerment: managing psychosocial aspects of diabetes (9 items); assessing dissatisfaction and readiness to change (9 items); and setting and achieving goals (10 items) [64]. It has been translated into various languages, and is considered a suitable tool in evaluating empowerment-based education programmes. The subscale on setting and achieving goals will be included as primary outcome. The Patients’ Evaluation of Quality of Diabetes Care is a 14-item scale assessing patients’ judgements about the quality of their diabetes care, which was found to be suitable for care delivered by physicians as well as nurses [64]. The Beliefs about Medication Questionnaire comprises two sections: the BMQ-Specific, which assesses representations of medication prescribed for personal use, and the BMQ-General, which assesses beliefs about medicines in general [66]. It has been translated into Dutch and used in many studies. The BMQ-Specific assesses beliefs about the necessity of and concerns about prescribed medication. The BMQ-General assesses beliefs that medicines are harmful and overused. The Problem Areas in Diabetes (PAID) is a 20-item questionnaire available in Dutch, assessing diabetes-specific emotional functioning [67]. The EQ-5D measures the general health status on five dimensions: mobility, self-care, daily activities, pain and symptoms, and negative emotions, and by a VAS-scale measuring overall health status on a scale from 0 to 100 [68].

### Process evaluation

In the post-intervention questionnaire, all patients will be asked to complete a checklist, which assesses contamination of control patients and exposure of intervention patients to the intervention. Intervention patients have to rate how easy or difficult they rate the decision aid information on a five-point Likert scale. Patients allocated to the computer version will in addition be asked how easy or difficult they rate its navigation properties. Since they will receive the paper version after the consultation, they will be asked for a comparison of the two versions. Providers’ experiences with the decision aid will be assessed in qualitative interviews using a topic list based on previous assessments regarding the implementation of innovations in practice. To assess adherence to the intended use (treatment fidelity), the actual use of the decision aid before and during consultations will be logged automatically in the computer version. In addition, all providers will be asked to complete a short checklist about the PORTDA-diab and the (shared) decision-making process after each consultation with an intervention patient.

### Data collection

Patient data will be collected with structured questionnaires and automated extraction procedures from the medical records. Patients’ empowerment, beliefs, satisfaction, and perceptions will be measured using mailed surveys that all patients will receive in the month before and 3 to 4 months after a scheduled quarterly consultation for diabetes. Data on actual management and clinical outcomes in the 6 months before and after the intervention period will be collected from the Groningen Initiative to Analyse Type 2 diabetes Treatment (GIANTT) database. This GIANTT database includes longitudinal data collected from primary care medical records using validated automated extraction procedures [69].

### Sample size

Sample size was calculated using the primary patient outcome, that is, change in diabetes empowerment scale (DES). Since there is no published minimum level of change considered to be relevant [70], we used a change of 0.2 in the DES score to estimate the sample size. With an expected range in its baseline value of 3.2 to 4.0, this represents a 5% to 6% change in the DES score. To be able to detect an absolute change of 0.2 in the DES score, a total of 150 patients per study arm is needed to achieve 80% power at 5% significance (standard deviation (sd) =0.62). It is therefore estimated that we will need a sample of 18 to 20 GPs, each with at least 20 to 30 participating diabetes patients. This number is expected to be sufficient to detect differences of 0.36 on the PEQ-D (sd=1.1), 6.5 on the PAID (sd=20.0), 0.26 on the BMQ (sd=0.8), and 5.0 on the UKPDS risk estimated (sd=15.5). These are all conservative sd estimates derived either from the original validation studies or available data on the UKPDS risk scores for the GIANTT population. Primary care practices in the recruitment region have on average around 45 type 2 diabetes patients eligible for this study.

### Statistical analysis

Descriptive statistics will be used to summarise demographic, clinical, and other patient measures. The primary analysis will test pre-post intervention changes in patient outcomes in the combined intervention group as compared to the control group using Student t-test and Wilcoxon’s two-sample statistics. Furthermore, we will examine differences in primary and secondary outcomes stratified by presentation format and medium in each intervention arm. For the process of care outcomes, z-approximation statistics will be used. Data will be analysed on an intention-to-treat basis, and results of two-sided tests between study arms will be regarded significant at *P*<0.05. We will explore the influence of the practice on the outcomes by multilevel modelling. Also, for hypothesis generation, interactions will be tested to identify possible factors at patient level that might modify the effect of the intervention.

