**Figure 2 F2:**
[figure not shown]
Practice randomisation scheme.

Within each practice, consenting patients will be randomised to receiving: (1) the PORTDA-diab presenting only CHD outcomes; (2) the PORTDA-diab presenting additional outcomes; or (3) the control group, using a blockwise scheme to conceal the allocation process for the healthcare provider. Although this design of randomising patients within practices has the disadvantage of potential contamination at provider level, it ensures that variations in communication skills and practice organisation are balanced between the intervention and control group. In addition, low participation and high drop-out rates can be expected when practices are randomised to a non-intervention control arm. It is not possible to use the PORTDA-diab for other patients than the intervention patients. It is, however, possible that providers will use some of the aspects learned from working with the novel approach in their usual care.

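### The primary analysis compares unadjusted DES change scores and names two tests without saying which decides; one baseline-adjusted model would be sharper at no cost

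*Protocol article*

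**What the plan says.** **Statistical analysis.** The primary analysis takes the pre-post change in patient outcomes and compares it "in the combined intervention group as compared to the control group using Student t-test and Wilcoxon’s two-sample statistics". Tests are two-sided at P<0.05. No covariate enters the primary comparison, and no rule says which of the two tests decides. The section also states "Data will be analysed on an intention-to-treat basis", and it plans multilevel modelling to explore the influence of practice.

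**Treatment allocation.** Practices are randomised to paper or computer. "Within each practice, consenting patients will be randomised to receiving" one of two versions of the aid or usual care, in blocks. No allocation ratio is given.

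**Sample size.** The calculation rests on change in the DES: "we used a change of 0.2 in the DES score to estimate the sample size". It concludes that "a total of 150 patients per study arm is needed to achieve 80% power at 5% significance", with "standard deviation (sd) =0.62". The text does not say whether 0.62 is the SD of one score or of the change. A later sentence on the SDs reads "These are all conservative sd estimates derived either from the original validation studies or available data". That hints at single-time SDs but does not settle the matter for the DES.

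**Data collection.** The questionnaires are mailed in the month before the consultation and again 3 to 4 months after it, so a baseline DES is collected by design.

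**The concern.** Two features of the stated analysis deserve a second look.

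First, a change score subtracts the whole of baseline, whatever the pre-post correlation. Regression on baseline estimates the coefficient instead, and its variance is never larger in large samples. The trial already collects the baseline score, so the precision lost buys nothing. If the correlation is low, the loss could take the primary comparison below the 80% power on which the trial was sized.

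Second, a t-test and a Wilcoxon test on the same outcome can disagree, and they address different hypotheses (means versus ranks). With no stated priority, the choice stays open until the data are seen. A favourable choice made then would raise the type I error above 5%.

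**Working it through.** **Inputs from the article:** difference 0.2, SD 0.62, 150 per arm, 80% power, two-sided 5%.

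**Assumed:** 1:1:1 allocation within practice, so the combined comparison is 300 v 150; equal pre and post variances; r from 0.3 to 0.8; practice intraclass correlation (ICC) from 0.01 to 0.10.

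**Step 1: the plan's own figure.** n per arm = 2 × (1.960 + 0.842)² × 0.62² / 0.2² = 151. Power at 150 v 150 is 79.8%. The stated 150 is reproduced.

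**Step 2: the planned contrast.** At 300 v 150, SE = 0.62 × √(1/300 + 1/150) = 0.062. Then 0.2/0.062 = 3.23, and 3.23 − 1.96 = 1.27, which gives 89.7% power if 0.62 applies to the quantity being compared.

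**Step 3: change score against ANCOVA.** With single-time SD σ, Var(change) = 2σ²(1−r) and Var(ANCOVA) = σ²(1−r²). The ratio is (1+r)/2.

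*Reading A: 0.62 is a single-time SD*

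| r | variance ratio | SD change / ANCOVA | power, 300 v 150 | n per arm, 1:1, 80% power |
|---|---|---|---|---|
| 0.3 | 0.65 | 0.734 / 0.591 | 78% v 92% | 212 v 138 |
| 0.5 | 0.75 | 0.620 / 0.537 | 90% v 96% | 151 v 114 |
| 0.7 | 0.85 | 0.480 / 0.443 | 98.6% v 99.5% | 91 v 77 |
| 0.8 | 0.90 | 0.392 / 0.372 | above 99% for both | 61 v 55 |

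The Sample size section allows as few as 18 × 20 = 360 patients, or 240 v 120. Power is then 68% v 86% at r=0.3 and 82% v 91% at r=0.5.

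*Reading B: 0.62 is the SD of the change*

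The change score has 89.7% power at every r. The ANCOVA SD is 0.62 × √((1+r)/2) = 0.500, 0.537 and 0.588 at r = 0.3, 0.5 and 0.8. Power is 97.9%, 96.1% and 92.5%. The number per arm (1:1) falls from 151 to 99, 114 and 136.

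**Step 4: if either test may count.** In 20,000 simulated null trials of 300 v 150, each test alone rejects in about 4.5% to 5.1%. At least one rejects in 5.9% (normal data), 6.1% (normal, rounded to 0.1), 7.3% (t with 3 df) and 7.9% (lognormal).

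**Step 5: leaving out practice.** With 19 practices of 24 patients randomised 2:1 within practice, the unadjusted t-test has a type I error of 4.8%, 4.5% and 4.0% at ICC 0.01, 0.05 and 0.10. Adjustment raises power from 89.7% to 90.0%, 91.1% and 92.5%.

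**The case against.** The strongest defence is that nothing here is invalid. The sample size and the analysis both rest on change, and a change score compared between randomised groups is unbiased. A reader might infer that baseline information is discarded. It is not: it enters with coefficient 1. The power loss also depends on values that the article does not give. Under Reading A it is negligible at r of 0.7 or more. Under Reading B the planned contrast has about 90% power without any adjustment. This stands, and it limits the point to efficiency.

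On the two tests, the sentence covers patient outcomes in general. It may mean a t-test for roughly normal scales and a Wilcoxon test for skewed ones, so two P values for the DES is a possible reading and not the only one. The article never says that either result may claim success. Even so, it does not tell the reader which test applies to the DES, and that gap remains.

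On practice, a reader might infer that omitting it inflates the type I error. Because patients are randomised within practice, the effect is slightly conservative (Step 5), and multilevel modelling is planned as exploration.

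A reader might also infer that patients with one questionnaire are dropped, against the intention-to-treat statement. The article does not say so. A change needs both scores unless imputation is used, but missing-data rules commonly sit in a full protocol or analysis plan, which is not shown. No finding rests on that here.

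**Conclusion.** The point holds as an efficiency gain and a clarification. As stated, the primary analysis is an unadjusted change-score comparison with two named tests and no deciding rule for the DES.

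Baseline adjustment would cut the variance by 35%, 25% or 10% at r = 0.3, 0.5 or 0.8. The gain in power at 300 v 150 runs from about 14 percentage points (r=0.3, Reading A) to almost none (r=0.8, Reading A). Under Reading B it is about 3 to 8 points. The change score falls below 80% power only under Reading A with low r, or with fewer patients. The two-test ambiguity is worth at most a type I error of about 6% to 8%, and only if either result may count. Practice adjustment adds 0.3 to 2.8 points of power.

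These sizes rest on assumed allocation, correlation and ICC, and on an SD whose meaning the article leaves open. The variance ratio (1+r)/2 needs only equal pre and post variances. The documents do not support a stronger charge of bias, discarded data or a broken intention-to-treat analysis.

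**What to change.** Name one primary analysis: a linear model of the follow-up DES Setting and Achieving Goals score on combined intervention versus control, adjusted for baseline DES, with practice as a fixed or random effect because patients are randomised within it. Report the adjusted mean difference with its 95% CI, and let that model's P value alone decide. Keep the Wilcoxon test on the changes as a sensitivity analysis. Use the same model for the continuous secondary patient outcomes. State whether 0.62 is the SD of a single score or of the change.

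The cost is a few sentences and no new data. The change should be fixed before outcomes are compared by arm, because a later choice between tests cannot be shown to be independent of the result.

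### For lipid-lowering treatment (i) and RAAS inhibitor use in albuminuria (j), the named z-test gives no role to pre-intervention treatment status, which is collected; read as a post-only comparison it is valid but imprecise

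*Protocol article*

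**What the plan says.** The Statistical analysis section covers the process outcomes in one sentence: "For the process of care outcomes, z-approximation statistics will be used". For the patient outcomes, the same paragraph is more specific: "The primary analysis will test pre-post intervention changes in patient outcomes in the combined intervention group as compared to the control group". No such reference to change is made for the process outcomes.

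The Outcome measures section defines (i) as "percentage of patients treated with lipid-lowering drugs" and (j) as "percentage of patients with (micro)albuminuria treated with a RAAS inhibitor". Neither refers to earlier treatment. The other two process outcomes are built differently. Outcome (g) is "percentage of patients with (intensified) antihypertensive treatment after insufficiently controlled blood pressure levels" and (h) is "percentage of patients with (intensified) glucose-lowering treatment after insufficiently controlled HbA1c-levels", so both count a start or step-up following an uncontrolled value.

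The Data collection section states that the earlier treatment record will be available: "Data on actual management and clinical outcomes in the 6 months before and after the intervention period will be collected".

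Under Treatment allocation, patients are randomised within practice to two versions of the aid or to control. Practice enters the analysis only through a multilevel model described as exploratory.

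**The concern.** The aid is tied to one quarterly consultation. The percentage of patients on a drug class some months later is therefore largely settled by who was on it beforehand. That variation is the same in expectation in both arms and carries no information about the aid. In a two-sample comparison of post-intervention percentages it still counts in full as noise.

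Research question 1f asks whether the aid changes treatment decisions, and (i) and (j) are two of the four outcomes that answer it. If they are analysed in the least precise way, a real change in prescribing could easily go undetected and be reported as no effect on treatment, although the data to sharpen the comparison are already held.

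**Working it through.** **The plan's own sample size.** n per arm = 2(1.96 + 0.842)² × 0.62² / 0.2² = 2 × 7.85 × 0.3844 / 0.04 ≈ 151, against 150 stated. This reproduces. It concerns the empowerment score; no rate or power is given for any process outcome.

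**Inputs.** From the article: 150 per arm, two intervention groups and one control group within practice, two-sided 5%. Assumed: equal allocation (150 control v 300 combined intervention); a share b already treated of 50%, 65% or 80%; 97% of treated patients persisting; 15% (control) v 30% (intervention) of untreated patients starting.

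**Formulae for outcome (i).**
- Percentage treated afterwards: p = 0.97b + (1 − b)u, where u is the starting rate. The difference is d = 0.15(1 − b).
- Plain test: patient variance p(1 − p).
- Test stratified on baseline treatment: patient variance b × 0.97 × 0.03 + (1 − b)u(1 − u).
- Power ≈ Φ[(d − 1.96 SE₀)/SE₁]. SE₀ uses the pooled rates (pooled u = 0.25) with 1/150 + 1/300 = 0.01. SE₁ uses each arm's own rates.

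**Worked case, b = 65%.** p = 0.6305 + 0.0525 = 0.683 in control and 0.6305 + 0.105 = 0.7355 in intervention, so d = 0.0525. The pooled p is 0.718.
- Plain: SE₀ = √(0.718 × 0.282 × 0.01) = 0.0450. SE₁ = √(0.2165/150 + 0.1945/300) = 0.0457. Power = Φ[(0.0525 − 0.0882)/0.0457] = Φ(−0.78) ≈ 22%.
- Stratified: pooled variance 0.0189 + 0.35 × 0.25 × 0.75 = 0.0845, so SE₀ = 0.0291. SE₁ = √(0.0635/150 + 0.0924/300) = 0.0270. Power = Φ[(0.0525 − 0.0570)/0.0270] = Φ(−0.17) ≈ 43%.

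**All three cases.** The simulated columns come from 20,000 trials per setting, with a Mantel-Haenszel test as the stratified analysis.

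| Already treated | Treated afterwards, control v intervention | Plain z, formula | Plain z, simulated | Stratified, formula | Stratified, simulated |
|---|---|---|---|---|---|
| 50% | 56.0% v 63.5% | 34% | 34% | 64% | 64% |
| 65% | 68.3% v 73.6% | 22% | 22% | 43% | 44% |
| 80% | 80.6% v 83.6% | 13% | 13% | 22% | 21% |

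Simulated type I error is near 5% for both tests. The ratio of pooled variances, plain to stratified, is 0.2379/0.1083 = 2.2, 0.2025/0.0845 = 2.4 and 0.1437/0.0608 = 2.4. Stratifying is thus worth about as much as doubling the sample.

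**Other assumed rates.** With 2% stopping and 10% v 30% starting, simulated power is 0.54 v 0.92 at 50% already treated, 0.40 v 0.83 at 60% and 0.19 v 0.42 at 80% (plain v stratified). With 10% v 20% starting at 60%, it is 0.13 v 0.33. Over 40–80% already treated, 5–10% starting in control and 0–5% stopping, baseline status explains about 67% to 94% of the control-arm variance.

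**Outcome (j).** The same reasoning applies, but the article does not give the number of patients with albuminuria. No power is computed; the absolute level would be lower in a subgroup.

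**The case against.** The strongest reply is that the sentence does not commit to post-intervention percentages. The trial is described as a pre-post design, and a z-test on within-patient change fits the wording. Under the same assumptions that test has power of about 64%, 44% and 23%, which recovers the loss. This stands: the loss belongs to one reading. It does not remove the point, because change is named for the patient outcomes and not for these. The wording also admits a test that treats the before and after percentages as independent, for which simulated power is 3% or less.

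Several stronger readings are tempting, and the article does not support them.
- A reader might infer that all four process outcomes ignore earlier treatment. Outcomes (g) and (h) build prior control and the treatment change into their definitions.
- A reader might infer that the denominators of (g), (h) and (j) use values measured after randomisation. Nothing says so, and measurement windows are detail that an article may leave to the full protocol.
- A reader might infer that practice is ignored altogether. It appears in an exploratory multilevel model, and since patients are randomised within practice, leaving it out of the simple test does not bias the comparison.
- A reader might want starts among untreated patients to become the main result. That would change the stated outcomes. It would also hide informed stopping, which is possible because the aid presents doing nothing as an option.

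It is also fair to say that these are secondary outcomes with no power claim, and that at 80% already treated even the better analysis reaches only about 21%.

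**Conclusion.** The point holds for outcomes (i) and (j). The named method gives no role to a strongly prognostic baseline variable that the trial collects. If post-intervention percentages are compared, power for (i) is about 34%, 22% and 13%, against 64%, 44% and 21% with stratification, at 50%, 65% and 80% already treated.

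The direction is secure wherever most patients keep their earlier treatment status. The size rests on assumed rates and on equal three-way allocation. For (j) the argument is qualitative.

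This is lost precision on secondary outcomes. A reader might take it for bias or an inflated false-positive rate; randomisation within practice and the simulated type I error near 5% rule that out. It is a worthwhile improvement, and the primary analysis is untouched.

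**What to change.** In the Statistical analysis section, replace the z-test for (i) and (j) with one of two analyses, each adjusted for treatment status in the 6 months before and for practice:
- a Mantel-Haenszel risk difference stratified on both. With 18 to 20 practices and two baseline groups there are 36 to 40 strata, or about 11 to 13 patients each if 450 are analysed; the method tolerates such sparse strata.
- a logistic model with both terms, converted to a difference in percentages so that the result still answers the stated outcome.

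Keep (i) and (j) as defined. Report starts among patients untreated before, and stops among those treated before, as supportive results by arm. On baseline treatment, (g) and (h) need no change.

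The cost is a change of wording and a slightly longer analysis. The treatment records before and after are already part of the planned extraction from the GIANTT database.

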### Research questions

1. What is the effect of the PORTDA-diab compared to usual care on:

a) patient empowerment (primary outcome)

b) beliefs about treatment options

c) negative emotions

d) satisfaction with care

e) perceived health status

f) treatment decisions

g) intermediate treatment outcomes and predicted coronary heart disease (CHD) risk

2. To what extent is the effect modified by the presentation medium or format:

a) comparing a paper-based with a computer version

b) comparing a short version presenting treatment effects on CHD risk with an extended version presenting effects also on other outcomes which can be of concern to patients

3. To what extent do healthcare providers and patients adhere to the intended use of the decision aid, and what are their experiences with using it in practice?

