### Treatment allocation

For pragmatic reasons, participating practices will be randomly allocated to the paper-based or computer version. This randomisation will be stratified by practice size (below or above 2,500 patients) and organisation (single or more primary care physicians), using a 1:1 computer-generated allocation sequence within the strata (Figure 2).

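### Paper versus computer is randomised by practice, but the plan names no test for that contrast that allows for practice

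*Protocol article*

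**What the plan says.** The trial randomises at two levels. Under Treatment allocation, "participating practices will be randomly allocated to the paper-based or computer version", "using a 1:1 computer-generated allocation sequence within the strata". Patients are then allocated to the short version, the extended version or control: "Within each practice, consenting patients will be randomised to receiving". The Research questions section lists the medium contrast as question 2a, "a) comparing a paper-based with a computer version", under a question about modification of the effect. The Objectives section makes presentation format a secondary aim.

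The Statistical analysis section tests the "combined intervention group as compared to the control group using Student t-test and Wilcoxon’s two-sample statistics". It gives a z-approximation for the process-of-care outcomes. Differences by format and medium are to be examined by stratification within the intervention arms, and no test is attached to that sentence. One rule covers everything: "results of two-sided tests between study arms will be regarded significant at" P<0.05. Practice appears once: "We will explore the influence of the practice on the outcomes by multilevel modelling". Interaction tests are planned for hypothesis generation and are described for patient-level factors.

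The Sample size section states that "a total of 150 patients per study arm is needed to achieve 80% power at 5% significance", for a 0.2-point change in the Diabetes Empowerment Scale (DES) with SD 0.62. It plans 18 to 20 practices with at least 20 to 30 patients each.

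**The concern.** For paper versus computer, the randomised unit is the practice. Patients in one practice share a provider, an organisation and a way of communicating, and the Treatment allocation section gives exactly this variation as a reason to randomise the other factor within practices. Medium lacks that protection: whatever distinguishes one set of 9 to 10 practices from the other set goes into the paper-computer difference.

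A t, Wilcoxon or z test that counts patients as independent gives such a contrast too small a standard error. A difference between two groups of practices could then be declared significant when the medium does nothing. The Discussion says the study will inform on differential effects of paper and computer versions, so the result will be reported and may guide later development.

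**Working it through.** **1. The plan's own figure.** Inputs from Sample size: difference 0.2, SD 0.62, two-sided 5%, power 80%.

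n per arm = 2 × [0.62 × (1.960 + 0.842) / 0.2]² = 150.9, so 151 against the stated 150. Power at 150 is 79.8%. The figure is reproduced, and it assumes independent patients.

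**2. Layout of the medium contrast.** Three within-practice groups of 150 make 450 patients, which fits 18 × 20 = 360 to 20 × 30 = 600. Assuming an equal three-way split, 300 receive the aid, 150 per medium. That is 300/20 = 15 aid patients per practice with 20 practices, or 300/18 = 16.7 with 18.

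**3. Error of a direct patient-level comparison of versions.** Design effect DE = 1 + (m − 1) × ICC, with m aid patients per practice. Actual error of a nominal 5% test = 2 × [1 − Φ(1.96/√DE)]. The ICC is an assumption. Example for m = 15, ICC 0.05: DE = 1 + 14 × 0.05 = 1.70; 1.96/1.304 = 1.503; error 13.3%.

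| Assumed ICC | DE, 20 practices (m = 15) | Error by formula | Error by simulation | DE, 18 practices (m = 16.7) | Error by formula | Error by simulation (m = 17) |
|---|---|---|---|---|---|---|
| 0.01 | 1.14 | 6.6% | 6.2% | 1.16 | 6.8% | 7.0% |
| 0.05 | 1.70 | 13.3% | 12.7% | 1.78 | 14.2% | 14.4% |
| 0.10 | 2.40 | 20.6% | 20.9% | 2.57 | 22.1% | 22.7% |

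At ICC 0 the simulated error is 4.9%. A t-test on practice means stays near 5% at every ICC. If versions are compared within one format only (m about 7.5), DE is 1.065, 1.325 and 1.65, and the error is about 6%, 9% and 13%.

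**4. Medium as a difference of effects.** Take the contrast (aid − control, computer) − (aid − control, paper). A practice effect common to aid and control patients cancels, leaving a true variance of (1 − ICC) times the one a patient-level test assumes. Error = 2 × [1 − Φ(1.96/√(1 − ICC))] = 4.9%, 4.4% and 3.9%. Simulation with 15 aid and 8 control patients in each of 20 practices gives 4.9%, 4.4% and 4.0%. Only variation between practices in the treatment effect itself would inflate this test.

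**5. Primary comparison.** Aid versus control is randomised within practice, so the same cancellation applies. Simulated error of the pooled t-test is 4.6%, 4.5% and 3.9% at ICC 0.02, 0.05 and 0.10: slightly conservative.

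**6. Precision of a valid direct medium test.** With 150 v 150 in 20 practices there are 20 − 2 = 18 degrees of freedom. SE = 0.62 × √(2 × DE/150). Power comes from the non-central t; detectable difference = (2.101 + 0.862) × SE.

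| Assumed ICC | SE | Power for 0.2 | Detectable difference (80%) |
|---|---|---|---|
| 0 | 0.072 | 75% | 0.21 |
| 0.01 | 0.076 | 70% | 0.23 |
| 0.05 | 0.093 | 53% | 0.28 |
| 0.10 | 0.111 | 40% | 0.33 |

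The ICC 0 row shows that about 5 points of power go to the small number of practices alone. With 18 practices, power is 68%, 50% and 37% at ICC 0.01, 0.05 and 0.10.

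**The case against.** The strongest reply is that the article never says medium will be tested with patient-level tests. It ties the t and Wilcoxon tests to aid versus control, and only speaks of examining differences by medium. A statistical analysis plan may supply the method, and multilevel modelling is already foreseen. This stands: a reader might infer a commitment to naive tests for medium, and the text does not go that far. What remains is that the article lists its tests, applies one significance rule to comparisons between arms, and gives the only method that allows for practice an exploratory purpose not linked to medium.

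The second reply is that question 2 asks about modification of the effect against usual care, and every practice has controls. Step 4 shows that on this reading a shared practice effect does no harm. This also stands. But the analysis section examines differences within the intervention arms and describes its interaction tests for patient-level factors, which medium is not. It does not adopt the protected contrast.

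Third, a reader might conclude that the sample size is wrong for lack of a design effect. It is not. It serves the primary outcome, whose comparison is made within practices, and the section claims no power specifically for medium.

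**Conclusion.** The concern holds in a limited form. For a practice-randomised factor that is a stated research question, the plan names only tests for independent patients and leaves practice to exploration. On the most natural reading, a direct comparison of aid patients between versions, the 5% error becomes about 6-7%, 12-14% and 21-23% at ICC 0.01, 0.05 and 0.10. These figures rest on an assumed ICC for change scores, equal practice sizes and an equal three-way split. The inflation is nil if that ICC is zero, smaller if versions are compared within one format, and absent for the difference-of-effects contrast unless practices differ in the treatment effect.

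It would be wrong to extend this to the primary comparison or to short versus extended: both are randomised within practice, and 150 per arm needs no design effect for them. Because medium is a secondary aim and its test is inferred, the severity is moderate.

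**What to change.** In Statistical analysis, state that every contrast involving medium, for patient and process outcomes alike, will be tested with practice as the unit of randomisation. Either of two analyses is enough: a mixed model with a random practice effect and small-sample degrees of freedom (about 16 to 18), or a test on practice-level summaries, using aid minus control where possible. Say which contrast answers question 2a: a direct comparison of versions, or a difference of effects against control.

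In Sample size, add that 80% power for 0.2 DES points does not apply to a direct medium contrast, and give its power and detectable difference over an assumed ICC range, as in step 6. Leave the 150 per arm unchanged.

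The cost is wording only, with no new data. The medium result will have wider intervals and a less favourable stated precision.
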